### Statistical Analysis

A flowchart will be provided for the non-SCOPE patients, presenting the number of patient data available, eligible/non-eligible for selection, the reason for being non-eligible, and if applicable, the numbers selected/not-selected based on propensity score matching with SCOPE patients.

The number (proportion) of SCOPE patients and non-enrolled patients (if applicable ‘propensity-score matched (PSM) selected’) will be presented stratified by country and health facility. The distribution of age, sex, body weight and primaquine dose will be presented in a Table for SCOPE patients (enrolled in post-implementation stage), and non-enrolled eligible patients (and if applicable, non-enrolled PSM-selected patients) to assess the balance of the distribution of age, sex and body weight.

If applicable, to determine the PSM selected patient dataset, the propensity score for SCOPE versus non-SCOPE eligible patients will be estimated using logistic regression with covariates age, sex, and body weight. This regression analysis will be conducted separately by country. We will then use the estimated propensity scores from each of these analyses separately for matching without replacement ‘m’ non-enrolled eligible patients to each SCOPE patient based on a distance that corresponds to ≤0.2 standard deviations of the estimated log odds of the estimated propensity score.

The risk that patients represent with *P. vivax* malaria within 6 months to the same health facility site (S2.SE18) will be analysed using survival analysis and visualised with Kaplan-Meier curves. The risk of recurrence will be determined for all SCOPE patients eligible for PQ treatment and non-SCOPE patients (and if applicable non-SCOPE PSM selected patients) administered PQ treatment. Multivariable Cox proportional hazards regression will be used to compare the SCOPE and non-SCOPE patients in the post-implementation period, controlling for calendar time at first visit (month) and seasonality (captured using splines) and a shared frailty of health facility. The validity of the proportional hazards assumption will be assessed visually using Schoenfeld residuals and stratified analyses will be conducted where the assumption is violated.

In the scenario that there are no substantial differences in the baseline characteristics between patients enrolled and not enrolled in SCOPE, propensity score matching will not be used for pseudo-randomisation and the Cox proportional hazards regression will adjust for age, sex and body weight, with shared frailty of health facility.

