### 3.1.1. Stage 1 – Preliminary safety and feasibility study

In Stage 1, the feasibility, safety and tolerability of point-of-care G6PD testing and PQ7 in G6PD normal (>70%) patients will be determined in 4 selected health facilities with staff undertaking clinical review on day 3 and also day 7 to ensure patient safety. Stage 2 will only proceed after review of the Stage 1 data by SRT and SMC.

After 3 months, the revised case management will be rolled out at 4 selected sites (2 in Indonesia and 2 in PNG), initiating Stage 1. The remaining sites will continue the Pre-Implementation Stage. Stage 1 is anticipated to last 6 months, during which a total of 800 patients with *P. vivax* malaria (~500 from Indonesia and ~300 from PNG) will be treated (Figure 1).

All patients that are eligible for and consent to participate in the study, will be tested by quantitative G6PD activity assessment using the G6PD STANDARD (SD biosensor, ROK). Patients with G6PD activity >70% ( $\geq 6.1$  U/gHb) will be prescribed primaquine at a total dose of 7 mg/kg over 7 days (PQ7) and those with 30-70% activity (4.1-6.0 U/gHb) will be prescribed the same total dose of primaquine over 14 days (PQ14). Patients with G6PD activity <30% ( $\leq 4.0$  U/gHb) will be prescribed primaquine at a dose of 0.75 mg/kg/week for 8 weeks (PQ8w).

The safety review team (SRT) will review all AESI (adverse event of special interest) and SAE (severe adverse event) data after every 100 patients treated with primaquine and may request to review additional data if there are safety concerns. A formal interim analysis is planned after enrolment of 400 patients (~150 patients from PNG, ~250 patient from Indonesia). The SRT will review the interim analysis outputs and share with the Safety Monitoring Committee (SMC) who will conduct an interim review and issue a recommendation regarding continuation of Stage 1.

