## 4 Sample size

### 4.1 Stage 1

In the Stage 1 preliminary study of the feasibility and safety of the implementation package, 4 health facilities will enrol 800 patients (~500 in Indonesia and ~300 in Papua New Guinea). Assuming 764 of these patients will have a G6PD activity >70% and be eligible for PQ7, and that the proportion of patients receiving short-course primaquine who have to stop therapy within 7 days is 5%, this sample size will produce a 95% confidence interval for the true proportion needing to stop treatment of +/- 1.55%.

### 4.2 Stage 2

**NOTE:** *Given slower than expected recruitment in Stage 1, the predicted patient recruitment in Stage 2 was revised down on 5 August 2024 to 70% of eligible patients (n=11,410) across Indonesia and Papua New Guinea. Additionally, an error was detected in the original power calculation for detection of a reduction in incidence of vivax malaria. In protocol vs 5.0, the total number of patients with vivax malaria recruited into the study was erroneously predicted to be 16,300 over 18 months (the initial timeframe for the study) when in reality this was the number of patients predicted over 12 months. This resulted in an underestimate of the monthly case incidence at each clinic and thus an underestimate of the power available for detection of an incidence reduction.*

*The revised and corrected power and precision calculations are provided below with the original erroneous calculations retained for reference. Power calculations for detection of an individual-level reduction in risk of vivax malaria recurrence are also provided.*

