#### 4.2.1 Revised and corrected Stage 2 power and precision calculations

Assumptions underlying the following Stage 2 power calculations include the following:

1. 5% of patients are ineligible for the intervention package (pregnancy, lactation, severe malaria, age <6m (Indonesia) or <1 yr (PNG)).
2. The impact on the risk and rate of infection will be the same across different endemic sites.
3. The mean baseline risk of *P. vivax* recurrence at 6 months is 20%
4. Loss to follow-up in both groups is 10%
5. Alpha = 0.05

During the 12-month pre-implementation period, a total of **17,160** patients with *P. vivax* (mono or mixed infections) presented to the ten study clinics (see Table 1). Assuming 5% of patients are ineligible for enrolment due to pregnancy, lactation or age under 6 months (Indonesia) or 12 months (PNG), this gives an estimated maximum number of patients eligible for recruitment into Stage 2 of **16,300**.

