### Dataset for Analysis

Endpoint S2.SE18 will include all SCOPE patients eligible for PQ treatment and a selected dataset of non-SCOPE patients who were treated with PQ treatment for *P. vivax* malaria according to national guidelines. SCOPE patients from both stage 1 and stage 2 will be included. The non-SCOPE patients will be eligible for selection if they were not enrolled in SCOPE at any stage (based on malaria card number and other identifying factors) and were administered the PQ dose according to national guidelines and met the SCOPE eligibility criteria: age >1 year (PNG) or ≥6 months (Indonesia, haemoglobin concentration ≥8 g/dl, and not pregnant or lactating and did not have severe malaria. Day 0 for non-SCOPE patients will be taken as the first visit by a patient following the stage 1 implementation date.

In the scenario that the baseline characteristics differ substantially between the SCOPE and non-SCOPE patients, a subgroup of these non-SCOPE patients will be selected for analysis using propensity score matching with the SCOPE patients. This will be done separately by country (PNG and Indonesia) and will be based on the following variables:- age, sex, body weight. Propensity score matching is a valuable way to control for bias and achieve pseudo randomisation in this exploratory analysis which is comparing SCOPE patients to routinely collected patient data.

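### S2.SE18: at the planned 70% recruitment there are too few non-SCOPE patients to match without replacement to each SCOPE patient, and the Cox model for that scenario leaves out age, sex and weight

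*SAP*

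**What the plan says.** SAP Section 11 compares recurrence within six months between SCOPE and non-SCOPE patients (S2.SE18). Both the dataset definition and the analysis text refer to all SCOPE patients eligible for primaquine, and "SCOPE patients from both stage 1 and stage 2 will be included". Non-SCOPE patients enter at their first visit after the Stage 1 implementation date. They must never have been enrolled, must have received primaquine according to national guidelines and must meet the SCOPE eligibility criteria.

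If baseline characteristics differ substantially, "a subgroup of these non-SCOPE patients will be selected for analysis using propensity score matching with the SCOPE patients". This is done separately by country on age, sex and body weight, by "matching without replacement ‘m’ non-enrolled eligible patients to each SCOPE patient based on a distance" of "≤0.2 standard deviations of the estimated log odds of the estimated propensity score". The section gives no value for m, no expected pool size and no rule for a SCOPE patient without a match.

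In the matched scenario the Cox model controls for calendar month, season and facility frailty. Section 7 waives adjustment for age, weight and sex once they have been considered in propensity score matching. Section 11 adjusts for them only when no substantial imbalance is found.

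On numbers, Section 4.2 says recruitment was "revised down on 5 August 2024 to 70% of eligible patients (n=11,410) across Indonesia and Papua New Guinea".

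**The concern.** Matching m comparators to each treated patient without replacement needs at least m usable comparators per treated patient. The wording about selecting a subgroup of non-SCOPE patients also presumes more comparators than SCOPE patients. When most eligible patients are enrolled, the position reverses: those not enrolled become the scarce group.

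Two things are at stake. If SCOPE patients without a match are left out, the estimate describes whichever SCOPE patients happened to find a partner. If they are kept, selection from a scarce pool takes nearly everyone in it and so balances little. The Cox model for that scenario then has no term for the three variables whose imbalance triggered the matching.

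**Working it through.** **Inputs and the plan's own figures**
- Section 4.2.1: 17,160 x 0.95 = 16,302; "this gives an estimated maximum number of patients eligible for recruitment into Stage 2 of" 16,300.
- Section 4.2: 16,300 x 0.70 = 11,410, as stated.
- Section 3.1.1: "Stage 1 is anticipated to last 6 months, during which a total of 800 patients", at four clinics (two per country).
- Table 1, eligible per year: Indonesia 13,210, PNG 3,092.

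**Pool from Stage 2 only, at 70% recruitment**
- Not enrolled: 16,300 - 11,410 = 4,890.
- Per Stage 2 SCOPE patient: 4,890 / 11,410 = 0.43.
- Per SCOPE patient with Stage 1 included: 4,890 / (11,410 + 800) = 4,890 / 12,210 = 0.40.
- By country, since matching is within country: Indonesia 0.3 x 13,210 / (0.7 x 13,210 + 500) = 3,963 / 9,747 = 0.41; PNG 928 / 2,464 = 0.38.

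**Adding non-SCOPE patients from the Stage 1 period**

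Assumptions: six months at Table 1 rates, any two Indonesian and two PNG clinics, 800 enrolled. Ratio = (4,890 + eligible at the four clinics over six months - 800) / 12,210.
- Lowest (Tanjung Leidong, Hanura, Baro, Napapar): eligible 1,690 / 2 = 845, adding 45; 4,935 / 12,210 = 0.40.
- Highest (Pasar Sentral, Wania, Mugil, Wirui): eligible 10,492 / 2 = 5,246, adding 4,446; 9,336 / 12,210 = 0.76.
- The ratio is below 1 in all 90 clinic combinations and above 0.50 in 72 of them.
- All ten clinics for six months: (4,890 + 8,150 - 800) / 12,210 = 12,240 / 12,210 = 1.00.
- If Stage 1 instead lasted 12 months at four clinics: 0.47 to 1.19.

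**Share of SCOPE patients that can be matched**
- m = 1: at most the ratio, so at least 24 to 60% have no match on the six-month, four-clinic range.
- m = 2: at most half the ratio, so only 20 to 38% could receive a full set.

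**Other recruitment levels (Stage 2 pool only; second figure with the 800 in the denominator)**
- 60%: 6,520 / 9,780 = 0.67; 6,520 / 10,580 = 0.62.
- 50%: 8,150 / 8,150 = 1.00; 8,150 / 8,950 = 0.91.

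These ratios come before the caliper and before the haemoglobin, guideline-primaquine and never-enrolled restrictions. The SAP does not quantify the resulting loss from the pool.

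**What matching achieves if all SCOPE patients are kept**

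In a simulation with one score and an assumed 0.3 SD imbalance, nearest-neighbour 1:1 matching without replacement within a 0.2 SD caliper selected nearly all comparators. The difference between all SCOPE patients and the selected comparators was 0.31 SD before and after at a ratio of 0.41. At a ratio of 0.76 it moved from 0.29 to 0.24 SD.

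**Power if only matched pairs are kept**

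Schoenfeld formula: power = Phi(sqrt(D x pi x (1 - pi)) x |ln HR| - 1.96), where pi is the SCOPE share. Expected events D = 0.95 x (n1 x p1 + n0 x p0), with p0 = 0.20 and p1 = 1 - 0.8^HR; the factor 0.95 counts half of the 10% loss to follow-up. With 11,410 per group and HR 0.9 it gives 92.4%, against 92% in Table 3.
- HR 0.9: 74% with 11,410 against 4,890; 60% with 4,890 pairs.
- HR 0.82, roughly the plan's 0.6 x 0.3 = 18% reduction: 99.7% and 98.4%.

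**The case against.** A reader might infer that there are fewer than 0.43 non-SCOPE patients per SCOPE patient, so that most SCOPE patients must go unmatched and 57 to 60% are discarded. The SAP does not support that. The figure of 0.43 covers Stage 2 alone, while the non-SCOPE pool opens at the Stage 1 implementation date, so 0.43 is not an upper bound. For m = 1, a majority unmatched depends on which clinics ran Stage 1 and for how long. Nor does any sentence remove an unmatched SCOPE patient: the selection and the flowchart concern non-SCOPE patients.

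Other points also stand in part:
- The 70% is a planning figure from August 2024. S2.SE18 was added in July 2025 because enrolment was lower than anticipated, and Section 11 gives no revised rate. Nearer 50%, 1:1 matching is close to feasible on counts alone, with little or no slack for the caliper.
- Matching is conditional on substantial imbalance, and the analysis is exploratory. The flowchart would make a shortage visible. Against this, matching is the only remedy the SAP names for substantial imbalance.
- The power loss is material only for HR 0.9 with a pairs-only analysis that the SAP does not specify. It is trivial at HR 0.82 or stronger effects, and the SAP claims no power for S2.SE18.
- Choosing weighting over matching is partly preference. The missing covariate adjustment in the matched scenario is not.

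**Conclusion.** The concern holds in this form. At 70% recruitment, with a six-month Stage 1 and its non-SCOPE pool drawn from the four Stage 1 clinics, there are 0.40 to 0.76 comparators per SCOPE patient before further restrictions. One match for each SCOPE patient without replacement is then impossible, and m of 2 or more cannot be completed for most. If all ten clinics count, the ratio is about 1.0. It passes 1 only under longer Stage 1 assumptions or recruitment at or below about half.

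Both ways of proceeding fail. Dropping unmatched SCOPE patients contradicts the stated inclusion of all those eligible for primaquine. Keeping them leaves most of the imbalance in place in a model without age, sex or weight, so measured confounding may go uncontrolled exactly when it is judged substantial. The size of the residual imbalance rests on the simulation's assumed 0.3 SD. Because the analysis is exploratory and conditional, this should be changed but does not threaten the trial's main conclusions.

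**What to change.** In Section 11, when baseline imbalance is substantial, replace 1:m matching without replacement by propensity-score weighting estimated within country, with robust variance, keeping all SCOPE patients. Weighting non-SCOPE patients to the SCOPE distribution does this directly. Full (variable-ratio) matching or matching with replacement would also serve.

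In every scenario, keep age, sex and body weight in the Cox model alongside calendar month, season and facility frailty, and delete the waiver in Section 7.

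If matching without replacement is retained, fix m, state the expected pool by country and by clinic and calendar window, and say how SCOPE patients without a match are handled.

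The cost is SAP wording and a different standard routine. Weights must be checked for extremes and robust standard errors used. No new data are needed.

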## 12 Quality Control Plans

Details of data cleaning and verification, including consistency and range checks, will be specified in a Data Management Plan.

## VARIABLES IN THE DATA SET

| Variable in data set          | Units                                              | Variable label                                                                                                      |
|-------------------------------|----------------------------------------------------|---------------------------------------------------------------------------------------------------------------------|
| Baseline/Enrolment CRF |                                                    |                                                                                                                     |
| scopeid                       | N/A                                                | SCOPE Study ID                                                                                                      |
| country                       | N/A                                                | Country                                                                                                             |
| staffid                       | N/A                                                | Staff Identification Number                                                                                         |
| studysite                     | N/A                                                | Study Site                                                                                                          |
| visitdat                      | N/A                                                | Visit Date                                                                                                          |
| mcad                          | N/A                                                | Indonesia: Malaria Card Number
PNG: Malaria ID                                                                   |
| initials                      | N/A                                                | Patient Initials                                                                                                    |
| sex                           | N/A                                                | Sex                                                                                                                 |
| age                           | years                                              | Age (years)                                                                                                         |
| agemonths                     | months                                             | Age (months)                                                                                                        |
| weight                        | kg                                                 | Weight                                                                                                              |
| pregnant                      | N/A                                                | Pregnant                                                                                                            |
| lactating                     | N/A                                                | Indonesia: Lactating < 6m
PNG: Lactating (infant younger than 12 months)                                         |
| village01                     | NA                                                 | Village of residence                                                                                                |
| village02                     | NA                                                 | Village of residence                                                                                                |
| ethnic                        | N/A                                                | Indonesia: Ethnic Group
PNG: Ethnicity                                                                           |
| ethnichigh                    | N/A                                                | Highland Papuan                                                                                                     |
| ethniclow                     | N/A                                                | Lowland Papuan                                                                                                      |
| ethnicoth                     | N/A                                                | Other Papuan (specify)                                                                                              |
| ethnicnon                     | N/A                                                | Non-Papuan (specify)                                                                                                |
| diagnostic                    | N/A                                                | Diagnostic                                                                                                          |
| ringform                      | N/A                                                | Ringform                                                                                                            |
| gametocyte                    | N/A                                                | Gametocyte                                                                                                          |
| diagnosis_ms                  | N/A                                                | Diagnosis (Microscopy)                                                                                              |
| diagnosis_rdt                 | N/A                                                | Indonesia: Diagnosis (RDT)
PNG: RDT test result                                                                  |
| g6pdtester                    | N/A                                                | Indonesia: Staff ID (G6PD Tester)
PNG: ID of staff conducting G6PD test                                          |
| g6pd                          | U/g Hb                                             | G6PD                                                                                                                |
| g6pdoor                       | N/A                                                | G6PD Out of Measuring Range                                                                                         |
| hbhc                          | U/g Hb                                             | Hb (Hemocue)                                                                                                        |
| hbhcoor                       | N/A                                                | Hb Hemocue Out of Measuring Range                                                                                   |
| hb                            | g/dL                                               | Hb                                                                                                                  |
| hboor                         | N/A                                                | Hb Out of Measuring Range                                                                                           |
| g6pdcat                       | N/A                                                | G6PD Category                                                                                                       |
| prescriber                    | N/A                                                | Indonesia: Staff ID (Prescriber)
PNG: ID number of prescriber                                                    |
| pqduration                    | N/A                                                | PQ Treatment Duration                                                                                               |
| pq                            | Tablets                                            | PQ (total tablets)                                                                                                  |
| pqobs                         | N/A                                                | Indonesia: 1 st dose PQ observed?
PNG: First dose PQ taken at facility                                |
| pqfood                        | N/A                                                | PQ taken with food?                                                                                                 |
| pqreas                        | N/A                                                | Indonesia: Reason 1 st dose PQ not observed
PNG: Reason 1 st dose PQ not taken             |
| pqreasoth                     | N/A                                                | Indonesia: Other reason 1 st dose PQ not observed
PNG: Other reason 1 st dose PQ not taken |
| dhp                           | DHP (total tablets)                                | DHP (total tablets)                                                                                                 |
| dhpobs                        | 1 st dose DHP observed?                 | 1 st dose DHP observed?                                                                                  |
| dhpreas                       | Reason 1 st dose DHP not observed       | Reason 1 st dose DHP not observed                                                                        |
| dhpreasoth                    | Other reason 1 st dose DHP not observed | Other reason 1 st dose DHP not observed                                                                  |
| al                            | AL (total tablets)                                 | AL (total tablets)                                                                                                  |
| txother                       | Other Treatment                                    | Other Treatment                                                                                                     |
| comments                      | Comments                                           | Comments                                                                                                            |
| Level 2 Review CRF     |                                                    |                                                                                                                     |
| scopeid                       | N/A                                                | SCOPE Study ID                                                                                                      |
| studysite                     | N/A                                                | Study Site                                                                                                          |
| l2_reviewdat                  | N/A                                                | Date of Review                                                                                                      |
| l2_reviewday                  | N/A                                                | Day of Review                                                                                                       |
| l2_reviewdayoth               | N/A                                                | Day of Review (other)                                                                                               |
| l2_location                   | N/A                                                | Location of Assessment                                                                                              |
| l2_locationoth                | N/A                                                | Location of Assessment (Other)                                                                                      |

